### Statistical analysis

Data will be analysed by a statistician blinded to group allocations, using the Statistical Package for the Social Sciences (SPSS) v. 22.0 (IBM). First, descriptive statistics will be executed, with calculation of means and standard deviations, and analysis of data distribution (by Shapiro-Wilk test) and evaluation of outliers. In case of normal data distribution, one-way ANOVA with repeated measures will be executed to analyse and compare changes in parameters between groups (with Bonferroni corrections for multiple comparisons). Relations between parameters will be examined by Pearson correlations. In case of non-normal data distribution, absolute changes in parameters will be compared between groups by Mann Whitney U-tests (with Bonferroni corrections for multiple comparisons). Relations between parameters will be examined by Spearman correlations. Statistical significance is set at *p* < 0.05, two-tailed. Observed statistical power will be calculated by use of GPower v. 3.1. Intention to treat analysis will be executed. Missing data will be handled using the last observation carried forward imputation technique. Dropouts and withdrawals from the study will be recorded through the intervention and follow-up periods. When differences in baseline phenotype are present, these differences will be taken into account during analysis of treatment effect between groups, by regarding them as co-variates.

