## Background

Approximately 640,000 coronary artery bypass graft (CABG) surgery procedures are performed in Europe and the United States each year to restore or optimize myocardial perfusion in coronary artery disease [1, 2]. Worldwide there are approximately over two million open-heart surgeries per year [3]. In this surgical intervention, venous and/or arterial grafts are used to bypass the coronary occlusion or stenosis. Because cardioplegia (induction of temporary cardiac arrest) is routinely used, the patient’s circulation is coupled to a cardiopulmonary bypass and access to the heart is most often achieved by median sternotomy. After CABG surgery, a hospital stay of 1 to 2 weeks is generally required [4, 5].

Although CABG surgery is an effective coronary revascularisation technique, there are a number of postoperative complications from which patients can suffer. For example, a decrease in pulmonary function is a frequently observed complication after CABG surgery. During the first week after CABG surgery vital capacity (VC) decreases by 30–60% [6–9] and even up to 1 year this remains reduced by 12% [10, 11]. Reduced VC has a negative effect on exercise tolerance (Vo2max) [12] and therefore it is important to optimize pulmonary function after CABG surgery. No method of postoperative therapy has been distinguished in treating or preventing these long-term changes [6].

In addition, Ragnarsdòttir et al. [8] found a diminished mobility of the left hemithorax at 3 months after CABG surgery. This decreased thoracic mobility was still present 12 months after surgery [11]. Thoracic mobility and vital capacity were affected more when the left internal thoracic artery (LITA)-retractor was used and reduced thoracic mobility is related to a diminished pulmonary function [10].

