### Outcome measures

Primary outcome measure will be the mean difference in change from baseline in SVC at 12 weeks after surgery between the two groups.

Secondary outcome measures will include:Change from baseline in SVC at 52 weeksChange from baseline in MacNew QLQ at 12 and 52 weeks after surgeryChange in pain from baseline on Visual Analogue Scale (VAS) at 12 and 52 weeks after surgeryChange in thoracic stiffness from baseline on VAS at 12 and 52 weeks after surgeryChange from baseline in maximal aerobic capacity (VO2max) at 12 weeks after surgery

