#### Spirometry

The Pocket-Spiro USB100 (Medical Electronic Construction & Logistic nv, Belgium) will be used for measuring pulmonary function. All patients are asked to perform a slow vital capacity (SVC) test, consisting of three measurements. For VC the best of the three measurements is used and for IVC the average of three measurements is used [49]. The instrument is calibrated prior to the test. When an OT is planned, SVC will be measured at least 2 days after OT, because the study wants to measure long-term effects (effects of the entire intervention), instead of any short-term effect (within the first hours after OT). SVC will be measured preoperative (-t_2_), 9^th^ postoperative day (-t_1_), 4 weeks after surgery (t_1_), 8 weeks after surgery (t_3_), 12 weeks after surgery (t_4_) and at 12 months after surgery (t_5_).

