### Sample size

A priori sample size calculation is based on pulmonary function (by GPower 3.1). The hypothesis for the OstinCaRe study is that the addition of OT towards endurance exercise training increases inspiratory vital capacity (IVC) by 12% during the follow-up of CABG patients. Power analysis is based on a 12% decrease in IVC at 12 weeks after surgery [11]. As a result, an increase of approximately 12% of the IVC is expected at 12 weeks after CABG. Sample size is computed considering an effect size of 0.50, a statistical power of 0.80 and an alpha level of 0.05. The power analysis outcome defines that 128 subjects per group are needed. Based on unpublished data of the cardiac rehabilitation centre a dropout rate of 20% is to be expected. Therefore, 154 subjects per group are needed. Participant recruitment began in January 2010 and is expected to finish in December 2017. Interim analysis is planned when 154 (50%) patients are included. The study can be stopped before reaching sample size if there is a significant change in surgery technique, which could compromise reproducibility and comparability throughout the study. The author makes the final decision to terminate the trial.

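### Last observation carried forward is the only missing-data method, although the protocol's own figures show that vital capacity changes over follow-up; the resulting bias at week 12 can go in either direction

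*Protocol article*

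**What the plan says.** The primary outcome, under Outcome measures, is fixed as follows: "Primary outcome measure will be the mean difference in change from baseline in SVC at 12 weeks after surgery between the two groups". Under Statistical analysis the article adds "Intention to treat analysis will be executed" and "Missing data will be handled using the last observation carried forward imputation technique". No second method and no sensitivity analysis is named. Under Sample size, "a dropout rate of 20% is to be expected".

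On the course of vital capacity, the Background says "During the first week after CABG surgery vital capacity (VC) decreases by 30–60" per cent and that "even up to 1 year this remains reduced by 12" per cent. The Sample size section says "Power analysis is based on a 12% decrease in IVC at 12 weeks after surgery".

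The Spirometry section schedules SVC before surgery, on postoperative day 9, at weeks 4, 8 and 12, and at 12 months. The questionnaire section schedules MacNew and the two visual analogue scales at t0, week 12 and 12 months only. The legend of Fig. 2 dates t0 to 3 weeks after surgery. The Osteopathic procedure section places the first treatment at week 4.

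**The concern.** Last observation carried forward (LOCF) assumes that a patient who leaves stays at the last measured level. The article's own numbers contradict this for vital capacity, which is deeply reduced just after surgery and much less so by week 12. A patient whose last SVC value is early therefore enters the primary comparison at a level the protocol expects to be temporary.

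For pain, stiffness and MacNew the problem comes from the visit schedule. There is no visit between t0 and week 12, so a missing week-12 value is replaced by t0 and the recorded change is exactly zero, whatever happened to the patient.

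If the arms differ in how many patients leave or when, these carried values turn into a difference between groups that is not a treatment effect. Unequal dropout is possible because only group B has four additional treatment sessions. LOCF is a stated choice, so this is not a detail left to a fuller document.

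**Working it through.** The plan gives no figure for the effect of LOCF, so I quantified the mechanism.

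**Inputs from the article**
- 154 per group (128 × 1.2 = 153.6) and 20% dropout, so about 0.20 × 154 = 31 patients per group with missing data.
- Mean deficit at week 12: 12%.
- First-week deficit: 30–60%; I also show 45%.
- Expected treatment effect: 12%; effect size 0.50.

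**Assumptions, not in the article**
- Standard deviation 12/0.50 = 24 points.
- Preoperative baseline.
- The first-week deficit applies on day 9, and the vital capacity and inspiratory figures apply to SVC.
- Dropout of 15% in one arm and 25% in the other (average 20%).
- For later dropout, linear recovery from day 9 to day 84.
- A normal-approximation comparison of the two week-12 means.

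**Formulas**
- Gap g = day-9 deficit minus 12, so 18, 33 or 48 points.
- Share of g still present: week 4, (84 − 28)/75 = 0.747; week 8, (84 − 56)/75 = 0.373; even split of the two, 0.56.
- False difference with no true effect: (0.25 − 0.15) × carried gap.
- Arm variance when all dropouts carry one visit: 24² + q(1 − q) × gap², with q the dropout share. For the even split, the spread between week-4 and week-8 values is added.
- Standard error: √[(V₁ + V₂)/154].
- Type I error: Φ(d/SE − 1.96) + Φ(−d/SE − 1.96).

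**Worked case, day-9 deficit 30%**
- d = 0.10 × 18 = 1.8.
- V₁ = 576 + 0.1275 × 324 = 617.3; V₂ = 576 + 0.1875 × 324 = 636.8.
- SE = √(1254.1/154) = 2.85; d/SE = 0.63; type I error 0.097.

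**Results with no true effect, 15% v 25% dropout**

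| Visit carried forward | Day-9 deficit 30% | 45% | 60% |
|---|---|---|---|
| All day 9 | 1.8 points, 9.7% | 3.3, 18.5% | 4.8, 28.0% |
| Half week 4, half week 8 | 1.0, 6.5% | 1.8, 9.8% | 2.7, 14.4% |
| All week 8 | 0.7, 5.7% | 1.2, 7.3% | 1.8, 9.6% |

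The arm that loses more patients looks worse. With 20% dropout in both arms and the same timing, the false difference is 0 and the type I error is 5% in every cell.

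**Direction with a true effect of 12 points, dropouts at the day-9 value**
- Control loses 25%, osteopathic arm 15%, deficit 30%: control mean 0.75 × (−12) + 0.25 × (−30) = −16.5; osteopathic mean 0.15 × (−30) = −4.5; difference 12.0. At a deficit of 60% it is −9.0 − (−24.0) = 15.0.
- Reverse split: −7.5 − (−14.7) = 7.2 at 30%, and −15.0 − (−19.2) = 4.2 at 60%.

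The same rule can therefore leave the estimate unchanged, inflate it, or remove well over half of it.

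**The case against.** **Dilution.** A reader might infer that LOCF dilutes any osteopathic effect. The article does not support that. As shown, the estimate is 12.0–15.0 points when control loses more patients. With equal 20% dropout at day 9 the estimate is 0.80 × 12 = 9.6 points, but those patients left before the first session at week 4. If only treated patients benefit, 9.6 is also the intention-to-treat effect. The article does not say that the target is the effect had everyone been treated.

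**Size.** The largest figures need every dropout to be last seen on day 9, and SVC is also measured at weeks 4 and 8. The article gives one dropout rate, with no split by arm or time, so the 15% v 25% split is mine. Both objections stand, which is why the range by timing matters more than its upper end.

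**Standard errors.** Imputed values are analysed as if observed, but with equal dropout the type I error stays at 5%. The illustration shows bias from unequal dropout and no separate standard-error failure.

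**Pain and quality of life.** A reader might infer a steep recovery here too. The article gives no course between week 3 and week 12. Only the zero change imposed by the schedule is established.

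**Baseline.** The article does not say whether baseline SVC is preoperative or day 9. With day 9, a patient last seen that day gets zero change. The mean bias is the same (completers gain 18 points in the 30% case, and 0.10 × 18 = 1.8), but the type I errors above would not carry over.

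None of this defends LOCF as the sole method. A bias of unknown sign cannot be called conservative.

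**Conclusion.** The point stands in this form: the sole prespecified missing-data method rests on a constancy that the protocol's own vital capacity figures contradict, and for the questionnaires it imposes zero change from a pre-treatment value. The direction of the bias cannot be predicted.

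Under the stated assumptions the false SVC difference runs from about 0.7 to 4.8 points, or 6–40% of the 12-point target (0.7/12 to 4.8/12). Type I error runs from about 6% to 28% depending on when patients leave, and is not inflated if dropout matches in amount and timing. These figures illustrate the mechanism and do not forecast this trial: the standard deviation, the split between arms and the recovery path are all assumed.

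**What to change.** Before allocation is unmasked for analysis, replace the LOCF sentence as follows.
- **SVC:** a likelihood-based mixed model for repeated measures using every observed visit of all randomised patients, with the between-group contrast at week 12 as the primary result. State which SVC measurement is the baseline.
- **Pain, stiffness and MacNew:** the same model or multiple imputation.
- **Sensitivity:** one delta-adjusted analysis that shifts the missing week-12 values by prespecified amounts, allowed to differ between arms. Keep LOCF, if at all, as a labelled sensitivity analysis.
- **Reporting:** give dropout by arm and by last visit attended, since the size of the problem depends on both.

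No new visits or data are needed, because the day-9, week-4 and week-8 SVC values are already scheduled. The cost is a change of wording, a little extra programming, and reliance on a missing-at-random assumption, which the delta-adjusted analysis is there to test. That assumption has least support for the questionnaires, where a patient lost before week 12 may have only the t0 value.

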### Randomisation and masking

Patients will be randomly assigned in a 1:1 ratio to either group A or group B (Fig. 1). A blocked allocation schedule will be used. Randomisation will be performed by means of opaque, sealed envelopes. A physical therapist of the cardiac rehabilitation centre will perform and store the randomisation. The personnel of the cardiac rehabilitation centre performing the outcome measurements in this study are unaware of patient’s allocation. Osteopathic treatments will not be performed in the presence of the personnel of the cardiac rehabilitation centre. The treatments will be performed in another location to assure that the personnel of the cardiac rehabilitation centre remains blinded to patient’s allocation. Only the treating osteopaths will be aware of the patient’s allocation. The enrolment and procedures are visualised in Fig. 2 according to the Standard Protocol Items: Recommendations for Interventional Trials (SPIRIT) guidelines [26, 27].

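### Covariates are chosen by observed baseline imbalance, so baseline SVC is not a prespecified covariate in the primary analysis and precision is forgone

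*Protocol article*

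**What the plan says.** The Outcome measures section defines the primary outcome: "Primary outcome measure will be the mean difference in change from baseline in SVC at 12 weeks after surgery between the two groups".

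The Statistical analysis section then gives two routes. With normal data, "one-way ANOVA with repeated measures will be executed to analyse and compare changes in parameters between groups". With non-normal data, "absolute changes in parameters will be compared between groups by Mann Whitney U-tests". Neither route names a covariate.

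The only rule on covariates in the article closes that section: "When differences in baseline phenotype are present, these differences will be taken into account during analysis of treatment effect between groups", with the differing variables entered as covariates. It does not say which variables make up the baseline phenotype, or what counts as a difference.

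On allocation, the Randomisation and masking section says: "Patients will be randomly assigned in a 1:1 ratio to either group A or group B". The schedule is blocked and no stratification factor is named.

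The Spirometry section schedules SVC preoperatively, on postoperative day 9 and at week 4, among other times, and does not say which of these is the baseline. The Osteopathic procedure section places the first treatment at week 4.

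**The concern.** In a properly randomised trial, any baseline difference between the groups is chance. A covariate earns its place because it predicts the outcome, and that can be judged before the data are seen. A rule that waits for the baseline table does the reverse: it may admit a variable that has nothing to do with SVC and leave out one that predicts it well.

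Two things are at stake. First, when no difference in SVC is declared, the primary comparison falls back on a change score. Subtracting baseline fixes its slope at 1, whereas ANCOVA estimates the slope, and the estimate is at least as precise. Second, because the criterion and variable list are open, whether the primary result is adjusted, and for what, is settled after the data are in hand.

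The rule also cannot be followed on the non-normal route, because a Mann-Whitney test has no place for covariates. This is a rule that the article states, not a detail left to an unseen analysis plan.

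**Working it through.** **Inputs.** From the article: 1:1 allocation; 128 per group before dropout and 154 enrolled per group; two-sided 0.05. Assumed, because the article gives no value: pre/post SVC correlation rho of 0.5, 0.7 or 0.9; equal SDs before and after (set to 1); a trigger of p<0.05. The article has no figure of its own on this point to reproduce.

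**Precision.**
- Variance of the change score: 2(1 − rho).
- Residual variance after ANCOVA on baseline: 1 − rho².
- Ratio: (1 − rho²) / [2(1 − rho)] = (1 + rho)/2.

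| rho | change score | ANCOVA | ratio | equivalent extra patients (1/ratio − 1) |
|---|---|---|---|---|
| 0.5 | 1.00 | 0.75 | 0.75 | 33% |
| 0.7 | 0.60 | 0.51 | 0.85 | 18% |
| 0.9 | 0.20 | 0.19 | 0.95 | 5% |

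**How often the rule fires.** With a p<0.05 trigger, baseline SVC enters in 5% of randomised trials. At least one of k independent baseline variables triggers with probability 1 − 0.95^k: 23% for k = 5, 40% for k = 10 and 64% for k = 20, whether or not that variable predicts SVC.

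**Simulation at 128 per group.** There were 20,000 trials under the null and 10,000 under an alternative set so that the change score has about 80% power (a difference of 0.35 change-score SD). The conditional rule uses ANCOVA only when baseline SVC differs at p<0.05. The free choice takes the smaller of the adjusted and unadjusted p-values.

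| rho | power: change score | power: always ANCOVA | power: conditional rule | type I: conditional rule | type I: free choice |
|---|---|---|---|---|---|
| 0.5 | 0.80 | 0.90 | 0.81 | 0.043 | 0.073 |
| 0.7 | 0.80 | 0.86 | 0.80 | 0.043 | 0.066 |
| 0.9 | 0.80 | 0.83 | 0.81 | 0.050 | 0.062 |

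The simulation standard error is about √(0.05 × 0.95/20,000) = 0.0015 for type I error and √(0.8 × 0.2/10,000) = 0.004 for power. The conditional rule keeps almost none of the ANCOVA gain, because it seldom fires.

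**One undeclared imbalance.** A 0.2 SD difference in baseline SVC at 154 per group gives z = 0.2 × √(154/2) = 1.755, p = 0.079, which a p<0.05 trigger would miss. It shifts that trial's change-score difference by 0.2 × (1 − rho): 0.10, 0.06 or 0.02 SD for rho of 0.5, 0.7 or 0.9.

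**The case against.** **Baseline SVC is already used.** It is subtracted in the change score, so a reader who infers that the plan ignores it goes too far. This stands: it is absent only as a covariate. Nor does the article support calling it the strongest predictor, since it reports no correlation. That is a general expectation.

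**The error rate is not shown to be wrong.** A reader might infer that a data-driven rule must inflate type I error. For a fixed p<0.05 trigger it does not: the simulated rates are at or below nominal. Inflation appears only if someone chooses between the two results, and the article assigns the analysis to a statistician blinded to allocation. This largely stands. Blinding makes it harder to choose by direction of effect, but coded groups still yield two p-values, and the article fixes no criterion that would rule out a choice between them.

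**The shift from an imbalance is not a bias.** This stands. Under randomisation the change-score difference is right on average; the 0.06 SD is conditional on one chosen imbalance. With no criterion stated, a 0.2 SD difference might in any case be declared.

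**Power is ample.** At the article's effect size of 0.50 and 128 per group, a two-sample t-test has 97.9% power, so on the plan's own figures the lost precision hardly threatens the test. This stands for the test. It does not make the interval as narrow as it could be: ANCOVA would multiply its width by √0.75 = 0.87, √0.85 = 0.92 or √0.95 = 0.97. The margin also disappears if the true effect is smaller than assumed.

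**The formula is simplified.** It treats one covariate and two time points with equal SDs, whereas the normal-data route is a repeated-measures ANOVA. The ratios are therefore a guide to size, not exact values for this trial.

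**Conclusion.** The point holds as one of efficiency and prespecification. The article states an imbalance-triggered covariate rule with no criterion and no variable list, and it prespecifies no covariate anywhere.

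The main harm is forgone precision: 5% to 25% of the change-score variance for rho from 0.9 down to 0.5, given equal SDs, with the conditional rule recovering almost none of it under a p<0.05 trigger. The secondary harm is an open analytic choice, worth a type I error of about 0.06–0.07 if it were exercised freely and partly limited by blinding.

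The documents do not support saying that the rule biases the treatment effect, that it inflates type I error when applied with a fixed trigger, or that the trial is underpowered because of it. The plan should be changed, but the trial is not invalid without the change.

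**What to change.** Delete the imbalance trigger and replace it with wording to this effect:

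- State which SVC measurement is the baseline. The preoperative and day-9 values both precede the first osteopathic treatment. The week-4 value is not assured to, since the Spirometry section asks for SVC at least two days after a planned treatment.
- The primary 12-week SVC comparison is an ANCOVA, or a repeated-measures model, that always includes pre-treatment SVC (preoperative, and optionally day 9), whatever the baseline table shows.
- For the primary outcome, the Mann-Whitney branch is replaced, or kept only as a sensitivity analysis, because it cannot take covariates.
- Each secondary outcome is adjusted for its own baseline value where that value is confirmed to precede the first treatment. VO2max needs this check: the Ergospirometry section first measures it at week 4, the same time point as the first treatment, and no order is given.
- Any adjustment prompted by observed imbalance is labelled exploratory.

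The cost for SVC is analysis wording only, as the preoperative and day-9 values are already scheduled. For VO2max the order of test and treatment must be checked in the records. The change should be dated and made before any comparison by group, including the interim analysis planned at 154 patients if that has not yet been run.
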